##### 4.3.1 Withdrawal Criteria

Reasons for study withdrawal may include but are not limited to:

- Noncompliance with study procedures.
- Physician's right to withdraw consent at any time during the study with or without stated reason.

##### 4.3.2 Documentation of Withdrawal of Subjects

The reason for withdrawal of any physician from the study will be appropriately documented.

## 5. TREATMENT OF SUBJECTS

The subjects are physicians. There is limited risk to participation. Risk would be loss of confidentiality and revelation of their score. Participants (physicians) will be informed of these risks and asked to provide IRB approved consent before participation. Participation is strictly voluntary. Subjects will be appropriately compensated for their participation in the study.

|                   |                                                                                                                 |                       |
|-------------------|-----------------------------------------------------------------------------------------------------------------|-----------------------|
|                   | Clinical Study Protocol                                                                                  |                       |
|                   | Title: Establishing the Clinical Utility (ECU) of First Step Dx PLUS and NextStep Dx PLUS |                       |
| Supersedes: Rev B | Document Number: Rev C                                                                                          |                       |
|                   | Effective Date: 11JUNE14                                                                                        | Page: 14 of 20 |

## 6. STUDY PROCEDURES

At enrollment, each eligible physician who agrees to participate will be assigned a unique subject identification number to be applied on all forms. Only the study team will have access to the subject's identity. The subject's name or other identifying information will not be used in analysis or reporting.

The main study procedures or assessments will include but are not limited to: collection of demographic and practice information during the screening process and completion of CPVs.

### 6.1 Pre-Screening and Eligibility

The evaluations for inclusion and exclusion criteria will include board certification, practice type and experience with FirstStepDx PLUS and/or NextStepDx PLUS.

### 6.2 Completion of CPVs™

Enrolled physicians will be provided a website address, user name and password to access the CPVs™. Each CPV™ is expected to take approximately 15-20 minutes. Participants will be given 7 days to complete the CPVs. If the CPVs are not completed within this time frame, the physician will be contacted and requested to complete the CPVs. Physicians will be reminded to complete the CPVs by phone calls and/or emails. If after 10 business days, they still have not completed the CPV, they will be withdrawn from the study.

## 7. STUDY DATA COLLECTION

Data entry and resolution will be performed in real-time concurrent with CPV data collection. All data will be linked to physicians via a unique identification number; only the study team will have access to their identities. Electronic data files will be password protected. Periodic audits will ensure data protection procedures are being followed. No physician will be mentioned by name in any data output.

## 8. STATISTICAL ANALYSIS

### 8.1 Determination of Sample Size

The study is adequately powered to detect differences in clinical practice patterns as measured by the CPVs. A sample size of 75 in each arm provides over 80% power to detect an estimated 6-7% difference in practice with alpha=0.05.

### 8.2 Planned Evaluations

Summary statistics will be determined for all variables. Simple cross tabulations will be prepared as part of the data resolution process. The calculation of basic descriptive statistics is used to check distributions and find outliers and out-of-range data. Numerical variables will be characterized in terms of means and standard deviations or by medians and interquartile range for skewed or highly non-normally distributed variables. For

|                   |                                                                                                                 |                       |
|-------------------|-----------------------------------------------------------------------------------------------------------------|-----------------------|
|                   | Clinical Study Protocol                                                                                  |                       |
|                   | Title: Establishing the Clinical Utility (ECU) of First Step Dx PLUS and NextStep Dx PLUS |                       |
| Supersedes: Rev B | Document Number: Rev C                                                                                          |                       |
|                   | Effective Date: 11JUNE14                                                                                        | Page: 15 of 20 |

hypothesis testing, tests will be conducted at a two-sided  $\alpha = 0.05$ . We have one primary outcome, quality as measured by the CPV.

#### *Baseline Data Analysis*

At baseline non-parametric estimates of differences will be calculated between the two groups (the control versus intervention groups to examine differences in CPV score and variance and utilization rates). Differences will be adjusted using multivariate and logistic regression models constructed to include age, gender, type of location (urban/suburban vs. rural), patients seen per week, practice size, single or multispecialty practice, practice ownership, and other practice characteristics and by patient characteristics such as type of payers, and use of biologics. Non-parametric estimates of differences in care utilization will be calculated and adjusted for physician, practice and patient characteristics described above.

Summary tables for each group will be generated for the following:

- Percent male
- Percent in single specialty practice
- Percent affiliated with an academic appointment
- Practice location
- Practice size (small, medium or large)
- Average days of week in practice
  - 1 to 2 days
  - 3 to 4 days
  - 5+ days
- Percent practices owned by
  - Physician group
  - Hospital
  - HMO
  - Community health center
  - Other
- Percent of patients covered by
  - Medicare
  - Commercial/Private
  - Medicaid
  - Self-pay / Uninsured
  - Other
- Mean (+/- 2 SD)
  - Years since fellowship
  - Number of patients with DD/ID seen per week
  - Age

#### Dependent/Outcome Variables:

- Behavioral
  - CPV® vignette score (overall and by domain)
  - Composite CPV diagnosis and treatment score

|                   |                                                                                                                 |                       |
|-------------------|-----------------------------------------------------------------------------------------------------------------|-----------------------|
|                   | Clinical Study Protocol                                                                                  |                       |
|                   | Title: Establishing the Clinical Utility (ECU) of First Step Dx PLUS and NextStep Dx PLUS |                       |
| Supersedes: Rev B | Document Number: Rev C                                                                                          |                       |
|                   | Effective Date: 11JUNE14                                                                                        | Page: 16 of 20 |

Main explanatory variables:

- FirstStepDx PLUS use
- FirstStepDx PLUS and NextStepDx PLUS use
- CPV® scores

Controlling for:

- Age
- Gender
- Number of years since fellowship
- Awareness of FirstStepDx PLUS and/or NextStepDx PLUS
- Practice location
- Practice size
- Type of location (urban/suburban vs. rural)
- Number of pediatric patients seen per week and number of DD/ID/ASD patients seen per week
- Number of physicians in practice
- Single or multispecialty practice
- Practice ownership (e.g., physician-physician group, community health center, etc.)
- Avg. type of coverage of patients (e.g., Medicare, Medicaid, etc.)

*Longitudinal Data Analysis*

With longitudinal data we can estimate the effect of FirstStepDx PLUS testing or the sequential use of FirstStepDx PLUS and NextStepDx PLUS testing on our primary and secondary outcomes. After the round 2 data is collected, we will conduct the longitudinal analysis incorporating type of intervention, time (before versus after), and the primary predictor, the time by intervention interaction (to look for differential changes over time). This allows a difference in difference analysis comparing differences between groups before and after intervention to assess the effect of FirstStepDx PLUS testing or the sequential use of FirstStepDx PLUS and NextStepDx PLUS testing.

Primary Outcome Variable:

- Quality of care (CPV® diagnosis/treatment score)

Secondary Outcome Variables:

- Use of appropriate therapy
- Utilization counts of laboratory tests and imaging studies ordered
- Overall CPV score

We will control for all potential confounders, including:

- Age
- Gender

|                   |                                                                                                                 |                       |
|-------------------|-----------------------------------------------------------------------------------------------------------------|-----------------------|
|                   | Clinical Study Protocol                                                                                  |                       |
|                   | Title: Establishing the Clinical Utility (ECU) of First Step Dx PLUS and NextStep Dx PLUS |                       |
| Supersedes: Rev B | Document Number: Rev C                                                                                          |                       |
|                   | Effective Date: 11JUNE14                                                                                        | Page: 17 of 20 |

- Number of years since fellowship
- Awareness of FirstStepDx PLUS and/or NextStepDx PLUS
- Practice location
- Type of location (urban/suburban vs. rural)
- Number of patients seen per week and number of DD/ID patients seen per week
- Number of physicians in practice
- Single or multispecialty practice
- Practice ownership (e.g. physician-physician group, community health center, etc)
- Avg. type of coverage of patients (Medicare, Medicaid, commercial, etc)

We will model CPV™ score as a continuous outcome variable in a multiple linear regression model, which controls for all potential confounders listed above. Our regression model is as follows, where CPV™ is the score for each physician, INTERV indicates type of intervention group and TIME indicates time period (pre and post-intervention).

$Y_{it}$  = CPVscore at time  $t$ , physician  $i$

$Y_{it} \sim Normal(\mu_{ijt}, \sigma_e^2)$

$\mu_{it} = \beta_0 + \beta_1 TIME + \beta_2 INTERV + \beta_3 TIME \times INTERV + \text{control variables}$

For binary outcome variables, for example use of biologic therapy, we will use a logistic regression model. Our regression is as follows, where INTERV indicates type of intervention group and TIME indicates time period (pre and post-intervention). For outcomes with a Poisson distribution, the distributional assumption would be changed from Bernoulli to Poisson and the link would be changed from logit to log. Otherwise, the basic modeling and analysis strategy will remain the same.

$Y_{it}$  = appropriate therapy  $t$ , physician  $i$

$p_{it}$  = probability of an outcome for time  $t$ , physician  $i$

$\text{logit}(E[Y_{it}]) = \beta_0 + \beta_1 TIME + \beta_2 INTERV + \beta_3 TIME \times INTERV + \text{control variables}$

For count outcome variables such as number of follow-up visits we will use log linear regression (i.e., using a log link in the analysis). Cluster re-sampled bootstrapping will be used to check model distributional assumptions.

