**Sample Size**

The study is adequately powered to detect differences in the combined diagnosis and treatment score as measured by the CPVs®. A sample size of 75 in each arm (225 total) provides over 80% power to detect an estimated 6-7% difference in scores with alpha=0.05. Due to possible attrition, extra subjects may be enrolled to ensure that at least 225 subjects will be used in the analysis.

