**Data Analysis**

Summary statistics will be determined for all variables. Simple cross tabulations will be prepared as part of the data resolution process. The calculation of basic descriptive statistics is used to check distributions and find outliers and out-of-range data. Numerical variables will be characterized in terms of means and standard deviations or by medians and interquartile range for skewed or highly non-normally distributed variables. For hypothesis testing, tests will be conducted at a two-sided  $\alpha = 0.05$ .

With experimental data we can estimate the effect of FirstStepDx PLUS or the sequential testing of FirstStepDx PLUS and NextStepDx PLUS on the primary outcomes comparing treatment and control groups. We will use a difference in difference analysis approach comparing differences between groups before and after intervention. We will control for all potential confounders, including physician-level characteristics, such as age, gender, specialty, years in practice, and practice-level characteristics—multi- versus single specialty practice, rural/urban location, and payor mix.

|                   |                                                                                                                 |                      |
|-------------------|-----------------------------------------------------------------------------------------------------------------|----------------------|
|                   | Clinical Study Protocol                                                                                  |                      |
|                   | Title: Establishing the Clinical Utility (ECU) of First Step Dx PLUS and NextStep Dx PLUS |                      |
| Supersedes: Rev B | Document Number: Rev C                                                                                          |                      |
|                   | Effective Date: 11JUNE14                                                                                        | Page: 9 of 20 |

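### The planned difference-in-difference is unbiased but uses the Round 1 score less efficiently than baseline-adjusted ANCOVA, and the written model omits within-physician pairing

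*Protocol*

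**What the plan says.** The Study Synopsis, under Data Analysis, commits to the method: "We will use a difference in difference analysis approach comparing differences between groups before and after intervention". Section 8.2, under Longitudinal Data Analysis, names the time-by-intervention interaction as the primary predictor and adds: "This allows a difference in difference analysis comparing differences between groups before and after intervention". The equation that follows has TIME, INTERV, their product and control variables, with normal errors of a single variance. It contains no physician term.

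The longitudinal list of control variables does not include the Round 1 score. CPV scores do appear among the main explanatory variables in section 8.2, but in a list that stands under the baseline analysis.

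On power, section 8.1 says: "A sample size of 75 in each arm provides over 80% power to detect an estimated 6-7% difference in practice with alpha=0.05". The synopsis says the same of the combined score: "provides over 80% power to detect an estimated 6-7% difference in scores with alpha=0.05". Neither place gives an SD, a correlation between rounds, or the estimator for which power was computed.

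**The concern.** Physicians are randomised to three arms (Synopsis, Study Design; section 2), so the expected Round 1 means are equal. There is then no need to subtract the Round 1 score with its coefficient fixed at 1, as a difference-in-difference does. Estimating that coefficient, as ANCOVA does, gives the same expected treatment effect with no more variance, and usually less.

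Round 1 is scored for every analysed physician, so any precision lost is lost for nothing. A modest correlation between rounds is possible, because each physician answers three open-ended vignettes drawn at random from nine (section 2.2). Below a correlation of 0.5, the change contrast is noisier than ignoring Round 1 altogether.

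The second matter is the model as written. If the two rows of one physician are treated as independent, the reported standard error does not benefit from the pairing on which a before-after comparison depends.

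**Working it through.** **Inputs from the protocol.** 75 per arm ("A sample size of 75 in each arm (225 total"), two-sided alpha 0.05, difference 6 to 7 points, power above 80%. **Not in the protocol:** the SD sigma of a score in one round, and the correlation rho between rounds. Both are treated as assumptions and shown over a range.

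**1. The plan's own figure.** It can be neither reproduced nor refuted without an SD. Solving backwards (normal approximation), 80% power needs a standardised effect of (1.960 + 0.842) × sqrt(2/75) = 0.4575. The analysed quantity must then have an SD of at most 6/0.4575 = 13.1 for 6 points, or 7/0.4575 = 15.3 for 7 points. The two ends of the stated range are not interchangeable: an SD that gives 80% at 7 points gives 67% at 6.

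**2. Variance of the treatment contrast**, in units of 2 sigma²/n, with equal variances in both rounds:

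- Round 2 score only: 1
- difference-in-difference, pairing modelled: 2(1 − rho)
- ANCOVA: 1 − rho²

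The ratio of ANCOVA to difference-in-difference is (1 − rho²) / [2(1 − rho)] = (1 + rho)/2, so the loss of information is (1 − rho)/2.

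| Assumed rho | Variance ratio | Loss | ANCOVA n per arm matching difference-in-difference at 75 |
|---|---|---|---|
| 0 | 0.50 | 50% | 37.5, so 38 |
| 0.3 | 0.65 | 35% | 48.75, so 49 |
| 0.5 | 0.75 | 25% | 56.25, so 57 |
| 0.7 | 0.85 | 15% | 63.75, so 64 |
| 0.9 | 0.95 | 5% | 71.25, so 72 |

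Simulation with 75 per arm gave variance ratios of 0.50, 0.66, 0.78 and 0.87 at rho 0, 0.3, 0.5 and 0.7, close to the formula.

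Equal variances matter for the size of the gain, not its direction. With SDs s1 and s2 in the two rounds, the variance factor is s1² + s2² − 2 rho s1 s2 for the difference-in-difference and s2²(1 − rho²) for ANCOVA. The difference is (s1 − rho s2)², which is never negative.

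**3. What this could mean for power (illustration).** Suppose that sigma is 13.1, the value at which a Round 2 comparison alone has 80% power for 6 points. At rho 0.3, 0.5 and 0.7 the difference-in-difference then has 66%, 80% and 95%, and ANCOVA has 84%, 90% and 97.5%.

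**4. The equation as written.** With independent rows and no control variables, the model takes the variance of the interaction as 4 sigma²/n. The true variance is 4 sigma²(1 − rho)/n. A nominal 5% test therefore rejects only when a standard normal variable exceeds 1.96/sqrt(1 − rho) in absolute value. The cut-offs are 2.34, 2.77 and 3.58 at rho 0.3, 0.5 and 0.7, giving a true type I error of 1.9%, 0.6% and 0.03%. Simulations of this set-up gave about 1.7% to 1.9%, 0.6% and no more than 0.1%. The test is conservative and loses power.

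**5. Role of the control variables.** Sections 4.3 and 9.2 drop the data of withdrawn physicians, so the analysed panel is in effect complete. In such a panel, time-invariant covariates entered as main effects leave the interaction estimate unchanged. They do reduce the residual variance, and so the reported standard error. If they explained half the between-physician variance (an assumption), the squared standard error would fall by the factor 1 − rho/2, to 0.85, 0.75 and 0.65 of 4 sigma²/n at rho 0.3, 0.5 and 0.7. The correct factor is 1 − rho, or 0.70, 0.50 and 0.30, so the standard error would still be too large.

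**The case against.** The primary endpoint is defined as a change from baseline, the difference-in-difference matches it in every place, and under randomisation it is unbiased. On that view this is a preference between two valid analyses. The validity part stands. It does not remove the point: the protocol fixes the less precise option when the better one uses data already planned. The endpoint need not be redefined either, because regressing the change on arm and Round 1 score gives exactly the same arm coefficient as regressing the Round 2 score on them.

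A reader might infer that the plan throws away a known share of its information, such as 15% to 35%. The documents do not support that: those figures belong to an assumed rho of 0.7 to 0.3, and no rho is given.

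A reader might also infer that the study is underpowered. That is not supported. The SD of 13.1 in the illustration is back-solved from a Round 2 comparison. If the sponsor used the SD of the change, a paired difference-in-difference has the stated power by construction. Even at 13.1 it reaches 80% at rho 0.5 and 95% at rho 0.7. The missing SD leaves power unverifiable for every estimator, ANCOVA included.

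It is fair, too, that the efficiency figures presume a paired analysis and so do not describe the equation as literally written. The cluster-resampled bootstrap in section 8.2 does not settle this, since it is offered only as a check on distributional assumptions.

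**Conclusion.** The point holds as a free improvement. For any rho below 1, with equal variances and pairing modelled, ANCOVA is more precise than the planned contrast, by a share of (1 − rho)/2. That share runs from 50% at rho 0 to 5% at rho 0.9, and where this trial falls is unknown. It would be wrong to call the planned analysis biased.

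The equation in section 8.2, taken literally, is a further weakness. Its standard error is too large for any positive rho unless the covariates capture all the between-physician variance. That costs power and does not inflate false positives.

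The claim of power above 80% is not shown to be wrong. It cannot be checked, because the SD, the correlation and the estimator are not stated.

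**What to change.** - Make the primary analysis an ANCOVA of the Round 2 combined diagnosis and treatment score on randomised arm, Round 1 score and specialty. Specialty is in the synopsis list of covariates but not in the longitudinal list of section 8.2, and the sample is planned as 70% specialists and 30% primary care. With one Round 2 row per physician, the pairing problem disappears.
- An equivalent choice is a longitudinal model with a common baseline mean (no INTERV main effect) and a within-physician correlation.
- Keep the difference-in-difference as a supporting analysis, with a physician-level term or cluster-robust standard errors, and correct the equation accordingly.
- Restate section 8.1 and the synopsis for the chosen model: the SD, the correlation, whether the 6 to 7 points are a Round 2 difference or a difference in change, and which end of that range is powered. For orientation, 80% power for 6 points by ANCOVA at 75 per arm needs a single-round SD of at most 13.1/sqrt(1 − rho²), or 13.7, 15.1 and 18.4 at rho 0.3, 0.5 and 0.7.

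The cost is wording in the analysis and sample-size sections. No extra physicians, vignettes or data are needed.

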Round 2 of data collection, or post-intervention assessment, will occur 4 weeks after the introduction of the intervention.

CPV scores will be used to compare baseline practice with practice post-intervention in the 3 different physician groups/arms.

This study will test the following hypotheses:

1. Clinical practice, specifically decisions around treatment of individuals with disorders of postnatal development including DD, ASD, and ID will vary widely among all physician types. This documentation of variation in practice will demonstrate the need for a new diagnostic service that FirstStepDx PLUS and NextStepDx PLUS would fulfill.
2. FirstStepDx PLUS and NextStepDx PLUS will improve the quality and appropriateness of care and therapeutic plans, as measured by the number of physicians that correctly act on the results of the assay.

This hypothesis will be tested through total of 9 CPVs consisting of 3 CPVs cases for each of 3 case archetypes as follows.

- Case A: Patients who are currently undiagnosed and for whom FirstStepDx PLUS or would initiate appropriate therapy
- Case B: Patients who are wrongly—or incompletely—diagnosed and for whom FirstStepDx PLUS would change therapy (i.e., terminate inappropriate or unnecessary therapy and initiate appropriate therapy)
- Case C: Patients who are undiagnosed by FirstStepDx PLUS testing and for whom NextStepDx PLUS testing would initiate appropriate therapy and/or earlier intervention will result in better outcomes

The CPVs™ will be randomly assigned to physicians for each to complete 3 CPVs™ (one from each type). Each of the CPVs™ will be scored by physicians for changes in clinical practice including treatment changes, frequency of follow up, laboratory tests and imaging studies ordered - see for scoring sheet.

|                   |                                                                                                                 |                       |
|-------------------|-----------------------------------------------------------------------------------------------------------------|-----------------------|
|                   | Clinical Study Protocol                                                                                  |                       |

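### Vignettes are randomly assigned, but the primary model has no vignette term; unless round 2 reuses the same cases, case difficulty stays in the error of TIME x INTERV and costs precision

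*Protocol*

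**What the plan says.** Protocol section 2.2 (Study Instruments) sets up the pool of cases: "This hypothesis will be tested through total of 9 CPVs consisting of 3 CPVs cases for each of 3 case archetypes as follows". The vignettes "will be randomly assigned to physicians for each to complete 3", one of each archetype. A second round follows in all arms four weeks after the intervention. Neither section 2.2 nor the synopsis says whether a physician then sees the same cases, a fresh random draw, or cases not yet seen.

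Section 8.2, under Longitudinal Data Analysis, states the primary model: "We will model CPV™ score as a continuous outcome variable in a multiple linear regression model, which controls for all potential confounders listed above". The mean for physician i at time t is an intercept plus TIME, INTERV, TIME x INTERV and the controls. Every listed control describes the physician or the practice. One residual variance is given and there is no physician effect. The distribution line carries a third subscript, j, that is never defined; the equation for the mean carries only i and t.

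On power, the synopsis says "The study is adequately powered to detect differences in the combined diagnosis and treatment score as measured by the CPVs", and section 8.1 says "A sample size of 75 in each arm provides over 80% power to detect an estimated 6-7% difference in practice with alpha=0.05". Neither gives an SD.

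**The concern.** Each score depends on the physician and on the cases drawn. If a physician's round 2 cases differ from the round 1 cases, the change between rounds includes how much harder or easier the second set was. TIME removes a shift in difficulty common to everyone. The part that differs between physicians, because they drew different cases, stays in the residual.

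The listed controls cannot take its place. They are fixed at baseline, and section 4.3 drops physicians who do not complete their vignettes, so the analysed panel has two rounds for everyone. In such a panel, main effects of time-constant covariates leave the TIME x INTERV estimate unchanged. The known design factor that may vary within a physician, the case set, is the one left out. What is at stake is the width of the confidence interval for the primary effect.

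**Working it through.** **Inputs.** From the protocol: 75 per arm, difference 6 to 7 points, more than 80% power, two-sided alpha 0.05, three archetypes with three cases each, one case per archetype per round. Assumed, because the protocol gives no figure: the SD of case difficulty within an archetype, tau (divisor 3), shown from 0 to 10 points.

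**Step 1, the plan's own figure.** It cannot be reproduced without an SD, so solve for the SD that gives 80% power at 6.5 points: SD = 6.5 / [(1.960 + 0.842) x sqrt(2/75)] = 6.5 / (2.802 x 0.1633) = 14.2. The t distribution gives 14.1, with 13.0 and 15.2 for differences of 6 and 7. I use 14.1 as the SD of a physician's change.

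**Step 2, case variance in the change.** A round's score is the mean of three cases, one per archetype.
- Cases redrawn independently: each round contributes 3 x tau²/9 = tau²/3, so the change carries 2 tau²/3.
- A different case of each archetype: two draws without replacement from three have covariance -tau²/2. The difference has variance 2 tau² + tau² = 3 tau² per archetype, and the change carries 3 x 3 tau²/9 = tau².
- Same cases: zero.

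**Step 3, ideal gain.** Take 14.1 to include the case noise. At tau = 8 with different cases, the remaining SD is sqrt(198.8 - 64) = 11.6. Then 6.5 / (11.6 x 0.1633) = 3.43, and 3.43 - 1.96 = 1.47, so power is about 93%. At tau = 5 the remaining SD is sqrt(198.8 - 25) = 13.2, giving about 85%. These figures ignore the cost of estimating the vignette terms.

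**Step 4, realised gain.** Simulation of the change-score analysis, 3,000 trials per setting, without versus with the six within-archetype vignette terms:

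| Case SD | Redrawn cases | Different cases |
|---|---|---|
| 3 | not in this run | 80% v 80% |
| 5 | 81% v 83% | 80% v 83% |
| 8 | 80% v 87% | 81% v 92% |
| 10 | 80% v 92% | 80% v 97% |

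Across simulation runs the change in power is about -1 to 0 points at SD 0 to 3, +1 to +5 at SD 5, +7 to +13 at SD 8 and +11 to +17 at SD 10.

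**Step 5, bias and error rate.** In a companion simulation (effect 6, other SD 13.1, tau = 8, different cases) the mean estimate without vignette terms was about 6.0. Under the null, type I error was 5.0% without the terms and 5.2% with them. With the same cases in both rounds, simulated power stayed at about 79 to 81%, so nothing was lost.

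**The case against.** **The loss depends on an unstated fact.** The protocol does not say that round 2 uses new cases. This stands, and the point is conditional on it.

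**Large gains need large assumptions.** Three evenly spaced cases with SD 8 or 10 span about 20 or 24 points within one archetype. At SD 10 with different cases, case choice makes up 100/198.8, or half, of the variance of the change. Nothing in the protocol supports or excludes this. It stands as a limit on size.

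**The power figures are not for the equation as printed.** They come from a change-score test. The printed model pools both rounds with one residual variance and no physician effect. If the within-physician correlation is assumed to be 0.5, a single score also has SD 14.1. The model then reports a standard error of 14.1 x sqrt(4/75) = 3.26, while the estimate's true SD is 14.1 x sqrt(2/75) = 2.30. That gives about 52% power and type I error near 0.5% with no case noise at all. This stands, and it is why the remedy must include a physician effect.

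**The matter is already covered.** The primacy-effect randomisation in section 2.2 concerns order, not difficulty. The control list is open-ended, but it speaks of confounders, and a randomly assigned vignette is not one. The undefined j might have meant case, yet no case term enters the mean. The cluster bootstrap only checks distributional assumptions. None of these answers the point. A separate statistical analysis plan could add the term, but the protocol writes the model out without it.

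**A stronger reading.** A reader might infer that the promised power is not delivered. If the planning SD left case noise out, power with different cases would be about 75%, 69% and 63% at case SD 5, 8 and 10. But the planning SD is not stated. If it came from data that already vary by case, the power claim stands and only efficiency is forgone.

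**Conclusion.** The point holds as a conditional loss of precision. Vignettes are randomly assigned, the written primary model has no vignette term, and unless round 2 reuses each physician's cases, case difficulty adds noise to the TIME x INTERV estimate. The gain from adding the terms is nil or slightly negative at a case SD of 0 to 3, modest at 5, and 7 to 17 points of power at 8 to 10. That rests on 75 per arm, an effect of 6.5, an SD of change of 14.1 including case noise, and a change-score analysis. The protocol does not fix where in this range the trial lies. A reader might also infer bias or an inflated error rate; random assignment of cases rules out both. The change is worthwhile because it is cheap and should be settled before scores are seen, not because the planned comparison is invalid.

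**What to change.** In section 8.2, fit the primary model to vignette-level combined diagnosis/treatment scores, with fixed effects for the nine vignettes, a physician effect, TIME, INTERV and TIME x INTERV. Alternatively, regress each physician's change score on arm and on indicators for the difference between the cases received in the two rounds. Adding vignette indicators to the printed equation without a physician effect is not a substitute. State in section 2.2 whether round 2 cases are the same as, redrawn from, or different from round 1, and define the subscript j or remove it.

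The cost is a short text change and six extra within-archetype parameters, or about one to two points of power if the cases prove equally difficult. Case identity must be kept in the analysis file. Vignettes are individually assigned and scored, so it should be available, but the protocol does not say that it is recorded.
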